**Methods:**

This is a prospective, 2-arm, open-label randomized controlled trial being conducted at the Department of Ophthalmology, Acharya Vinoba Bhave Rural Hospital, Sawangi, India. A total of 92 patients aged 35 to 75 years with intraoperative posterior capsular compromise will be randomized (block randomization, sealed opaque envelopes) into 2 groups: group A (retropupillary iris-claw IOL) and group B (scleral-sutured IOL). Preoperative, intraoperative, and postoperative data will be collected at day 1, day 15, day 30, and day 90. The primary outcomes are best-corrected visual acuity and lens-induced astigmatism at 3 months. Secondary outcomes include IOL centration or tilt, intraoperative and postoperative complications, and patient satisfaction (assessed using the National Eye Institute Visual Function Questionnaire-25). Data will be analyzed using ANOVA and mixed-effects models.

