### Hypothesis

This randomized controlled trial hypothesizes that retropupillary iris-claw IOL implantation will achieve visual outcomes (measured by best-corrected visual acuity [BCVA] and lens-induced astigmatism at 3 months) that are noninferior or superior to those obtained with scleral-sutured fixation. It is further hypothesized that the iris-claw technique will demonstrate shorter operative time and fewer intraoperative and postoperative complications, while maintaining comparable centration and patient-reported satisfaction scores.

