### Outcome Measures

Primary outcomes:

BCVA at 3 months using Snellen’s chart, converted to logMAR values for statistical analysis.Lens-induced astigmatism, measured through keratometry and autorefractometry.

Secondary outcomes:

Intraoperative complications (posterior capsular rupture extension, vitreous loss, surgical duration).Postoperative complications (hyphema, pigment dispersion, raised intraocular pressure, IOL decentration, cystoid macular edema).IOL centration and tilt, assessed by slit-lamp retroillumination following the method of Calzetti et al [10].Patient-reported satisfaction and visual function, measured using the National Eye Institute Visual Function Questionnaire-25 at 3 months.

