### Data Management and Statistical Analysis

Statistical methods used for data management and analysis are summarized in this section. Continuous variables (eg, BCVA, astigmatism, and intraocular pressure) will be summarized as mean (SD) and analyzed using the independent *t* test for between-group comparisons and repeated-measures ANOVA for longitudinal analysis. Categorical variables (eg, complications and sex) will be compared using the chi-square test or the Fisher exact test. Multivariate analysis will be performed using mixed-effects linear regression to adjust for baseline covariates (age and preoperative vision). Missing data will be handled using multiple imputation under a missing-at-random assumption. Interim analysis will be conducted after 50% enrollment to evaluate safety and adherence; no stopping rules for efficacy are planned. Statistical analyses will be performed using SPSS software (version 27.0; IBM Corp). A *P* value <.05 will be considered statistically significant.

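### Two equal primary outcomes are each tested at P<.05 with no rule for combining them; if either one can carry the conclusion, the chance of a false primary result rises to as much as 9.75%

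*Protocol article*

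**What the plan says.** The Methods paragraph of the abstract gives two primary outcomes: "The primary outcomes are best-corrected visual acuity and lens-induced astigmatism at 3 months". The Outcome Measures section lists them again, BCVA first and then "Lens-induced astigmatism, measured through keratometry and autorefractometry", and ranks neither above the other.

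The Hypothesis section covers both outcomes in one sentence. It expects the iris-claw lens to give results "that are noninferior or superior to those obtained with scleral-sutured fixation". It does not say what follows if the two outcomes disagree.

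The Data Management and Statistical Analysis section names BCVA and astigmatism among the continuous variables. It assigns them the independent *t* "test for between-group comparisons and repeated-measures ANOVA for longitudinal analysis". It then sets a single criterion: a P "value <.05 will be considered statistically significant". The article gives no division of alpha, no testing order, and no either-suffices or both-required rule.

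**The concern.** With two primary outcomes, a per-test threshold does not by itself settle what the trial may conclude. Two readings are open, and they have different consequences.

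- **Either outcome suffices.** There are then two chances of a false positive, and the error rate for the primary conclusion is above 5%.
- **Both outcomes are required.** The error rate is held, but significance on one outcome alone is not a positive trial, and the article does not say how it would be described.

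Disagreement between the outcomes is plausible. BCVA is measured after refractive correction, which removes regular astigmatism, so the arms could differ on astigmatism and not on acuity. Without a stated rule, the reading could be chosen once the results are known. Masking of assessors and analysts does not prevent that, because the choice can be made after unmasking.

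**Working it through.** **Inputs from the article.** Two primary outcomes (abstract; Outcome Measures). Per-test level .05 (Data Management and Statistical Analysis). 92 patients allocated 1:1, so 92/2 = 46 per arm. The interim look covers safety and adherence, with no efficacy stopping rule, so it adds no efficacy test.

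**Assumptions.** Two-sided tests (sidedness is not stated); approximately normal test statistics; the correlation r between them (not given); 80% power per outcome where power is used (the sample-size calculation is in an appendix that is not shown).

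**The plan's own figure.** The .05 is a chosen level, so there is nothing to reproduce. The total of 92 cannot be re-derived without the appendix.

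**Step 1: either outcome suffices, neither truly differs.** If independent, 1 − (1 − 0.05)² = 1 − 0.9025 = 0.0975. Whatever the correlation, the bound is 0.05 + 0.05 = 0.10. With correlation r, the probability is 1 − P(|Z₁| ≤ 1.96 and |Z₂| ≤ 1.96) under a bivariate normal:

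| r (assumed) | At least one false significant primary |
|---|---|
| 0 | 9.75% |
| 0.3 | 9.5% |
| 0.5 | 9.1% |
| 0.7 | 8.4% |
| 0.9 | 7.0% |

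**Step 2: both required.** Each test can stay at .05. The error of the joint claim is at most 5%, and is 0.05² = 0.25% if neither outcome differs and the tests are independent. The cost falls on power: with 80% each, joint power is 0.8² = 64% at r = 0 and 69% at r = 0.5.

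**Step 3: how often a split result would arise.** With 80% power on each outcome, exactly one test is significant with probability 2 × 0.8 × 0.2 = 32% if independent. With correlation it is 1.6 − 2 × P(both): 1.6 − 2 × 0.666 = 27% at r = 0.3, and 1.6 − 2 × 0.687 = 23% at r = 0.5.

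**Step 4: cost of testing at .025.** At 46 per arm, ignoring dropout, the difference detectable with 80% power is (z for α + 0.842) × √(2/46).

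- At .05: (1.960 + 0.842) × 0.2085 = 0.584 SD.
- At .025: (2.241 + 0.842) × 0.2085 = 0.643 SD.

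An effect with 80% power at .05 has power Φ(2.802 − 2.241) = about 71% at .025. Restoring 80% would take 46 × (3.083/2.802)² = 55.7, so 56 per arm or 112 in total.

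**Step 5: what a split achieves.** Two independent tests at .025 give 1 − 0.975² = 4.94%, and never more than 5%. Holm has the same bound under any correlation.

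**The case against.** The best defence is that a condensed article need not carry the success rule for two primary outcomes. An analysis plan or the sample-size appendix may hold it, and a per-test significance convention does not contradict a separate rule stated elsewhere. That is fair, and it limits how strongly the point can be put. It does not remove the point: the article does fix a threshold, applies it to both primary outcomes, and states a hypothesis covering both. A rule held elsewhere would have to qualify that text.

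A reader might infer something stronger: that the trial's main claim carries nearly twice a promised 5% error rate. The documents do not support that, for four reasons.

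- The .05 is a per-test level. The article claims no trial-wide rate.
- The inflation exists only if either outcome suffices. The single sentence in the Hypothesis section can be read as requiring both, and then there is none.
- High correlation lowers the figure, to about 7.0% at 0.9.
- The 9.75% counts false results in either direction. False superiority of iris-claw on at least one outcome has probability 1 − 0.975² = 4.9% if independent. That is about twice the one-directional 2.5%, but not above 5%. Nor does the figure describe a noninferiority claim, which these difference tests do not address.

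Both outcomes are also named in advance, so a split result would be visible to readers. The room for choosing a reading afterwards is real but limited.

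**Conclusion.** The point holds in conditional form. The article gives two primary outcomes of equal rank and a flat per-test threshold, with no rule for combining them. If either outcome can support the primary conclusion, the chance of at least one false significant primary result is up to nearly double 5%, at 9.75%; it is lower the more strongly the two tests are correlated. If both are required, the error rate is sound, but the article does not say so. Under either reading it does not say how a split result will be interpreted, and with 80% power on each outcome such a result would arise in roughly a quarter to a third of trials.

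The correlations and the 80% power are assumptions; the error figures also rest on two-sided tests. The matter should be fixed. It is not grounds for calling the analysis invalid.

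**What to change.** Before the final analysis, add to Outcome Measures and to Data Management and Statistical Analysis:

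1. Superiority on the two primary outcomes is tested by Holm: the smaller P against .025 and, only if that is met, the other against .05.
2. A significant result on one outcome is reported as a result for that outcome only.
3. Any joint claim about visual outcomes requires both outcomes to meet it.
4. A joint noninferiority claim also requires a prespecified margin for each outcome. The article shows none, so the claim cannot be made from what is written there.

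Holm is not the only valid choice. Naming one primary outcome, or requiring both at .05, would also close the gap if stated in advance.

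**Cost.** The change is one of wording and needs no new data. The Results section reports that no interim data had been analyzed at submission. The downside is power: an effect on one outcome only, with 80% power at .05 (assumed), has about 71% at .025, and 112 patients rather than 92 would be needed to restore it. Any power stated in the sample-size appendix should therefore be checked at .025 and restated if needed.

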### Ethical Considerations

The study was approved by the Institutional Ethics Committee of Datta Meghe Institute of Higher Education and Research (DMIHER(DU)/IEC/2024/24, dated May 3, 2024) and was prospectively registered with the Clinical Trial Registry of India (CTRI/2025/03/083687) on March 28, 2025. The trial will be conducted in accordance with the Declaration of Helsinki and Good Clinical Practice guidelines. Written informed consent will be obtained from all participants prior to enrollment. Participant privacy and confidentiality will be maintained, and all data will be deidentified prior to analysis and publication. Data will be recorded in standardized case report forms and entered into a secure password-protected database. All study data will be anonymized prior to analysis and dissemination. Personally identifiable information, including names and medical record numbers, will be removed or replaced with coded identifiers. The reidentification key will be stored separately in a secure, password-protected database accessible only to the principal investigator.

## Results

Patient recruitment began in March 2025 at the Department of Ophthalmology, AVBRH, Sawangi, India, with an estimated completion date of September 2025. As of this submission, participant enrollment and follow-up are ongoing, and no interim data have been analyzed. Preliminary observations indicate adherence to the standardized surgical protocol and follow-up schedule. Data collection for all preoperative, intraoperative, and postoperative variables, including BCVA, IOL centration, and patient-reported satisfaction, will continue as per the CONSORT flow framework. Final analysis and dissemination of results are expected by early 2026.

## Discussion

Management of aphakia during cataract surgery remains a critical surgical challenge, particularly when posterior capsular rupture or zonular instability precludes in-the-bag IOL implantation [11,12]. Although several fixation techniques have been developed, the comparative efficacy and safety of scleral-sutured and retropupillary iris-claw fixation during primary cataract surgery remain insufficiently explored [13]. This protocol aims to prospectively evaluate these two commonly used methods under standardized conditions. The rationale for comparing scleral-sutured and iris-claw fixation stems from their distinct anatomical and procedural advantages. Retropupillary iris-claw lenses offer a posterior chamber position similar to that of an in-the-bag IOL while avoiding contact with the corneal endothelium and anterior chamber angle [2,3]. They are relatively simple to implant, require shorter surgical time, and provide satisfactory centration with minimal postoperative astigmatism [5,7]. Conversely, scleral-sutured fixation restores a near-physiological IOL position behind the iris plane and has been associated with excellent visual outcomes and long-term stability [8]. However, it demands greater surgical skill and carries the potential of suture-related complications, including knot erosion and late dislocation [14,15].

Several retrospective and comparative studies have examined the outcomes of these techniques, but most involve heterogeneous populations or secondary IOL implantations. Madhivanan et al [5] demonstrated that both retropupillary iris-claw and scleral-fixated IOLs achieve significant improvement in BCVA, although scleral fixation required longer surgical duration. Similarly, Durmus et al [7] reported comparable visual outcomes but found that endothelial cell loss was lower with iris-claw lenses than with sutureless scleral fixation. Shahid et al [8] emphasized that scleral fixation provides superior long-term centration yet remains technically demanding and time-intensive. These findings justify the need for a prospective, randomized evaluation focusing specifically on primary cataract cases rather than secondary or complicated aphakia.

This trial’s methodological design addresses previous limitations by incorporating randomization, allocation concealment, and masked outcome assessment. Objective parameters such as IOL tilt and decentration will be evaluated using slit-lamp retroillumination and validated anterior-segment optical coherence tomography methods described by Calzetti et al [10], ensuring quantitative reproducibility. In addition, the inclusion of patient-reported outcomes using the National Eye Institute Visual Function Questionnaire-25 will provide valuable insights into subjective satisfaction and functional vision, which have often been underrepresented in earlier studies.

Ethical oversight, AE monitoring, and quarterly data review by an independent committee have been included to maintain methodological rigor and compliance with Good Clinical Practice guidelines. The statistical plan using mixed-effects modeling and repeated-measures ANOVA will allow robust analysis of longitudinal data while accounting for missing values. The trial does not include an economic analysis, as cost-effectiveness was beyond the scope of the present protocol; however, results regarding operative time and complication rates may have indirect implications for resource optimization in tertiary-care settings. Potential limitations of this study include its single-center design and limited sample size, which may influence external generalizability. Nonetheless, the use of standardized surgical techniques, strict eligibility criteria, and a uniform postoperative evaluation schedule are expected to enhance internal validity and reproducibility.
